### Participants and selection criteria

This study involves two groups of participants: parents/guardians of sick children and healthcare providers. Parents/guardians are eligible for inclusion in the study if they are accompanying children under 13 years of age for a sick child outpatient visit at a study facility on a day when we are recruiting patients; are 15 years of age or older; and provides informed consent or assent in the case of parents/guardians aged 15–17. For individuals who are 15–17 years old we will ask if they are either the parent or legal guardian of the child to ensure that they are emancipated minors. For individuals older than 18, all adults who accompanied the child, regardless of their relationship to the child are invited to participate. The relationship to the study child is determined during the survey. For a subset of parents/guardians we will invite them to participate in a follow-up phone survey ~1–2 weeks after their initial facility visit.

All skilled healthcare providers in the study facilities will be invited to participate in a structured interview that assesses their views on healthcare quality as well as their job satisfaction. A healthcare provider is eligible for inclusion in the study if s/he is working in a study facility; is a skilled provider (i.e., cadre is nurse, clinical officer, medical officer, or medical doctor); provides outpatient care for sick children; is 18 years of age or older; and provides informed consent.

### Sample size estimation

Our study sample will include 75 government-managed primary health facilities (25 facilities per arm). Our sample size calculations used data from the MNH+ study conducted in the same region in 2016 among 2,002 individuals at 12 health facilities as well as from the Tanzania Demographic and Health Survey 2015–16 (Larson et al., under review) (24). We conducted our sample size calculations based on two indicators of patient experience: disrespectful care and provider communication of child's diagnosis, using baseline prevalence and intraclass correlation coefficients (ICC) determined from the prior studies.

For each of the outcomes of interest we calculated the minimum detectable difference given alpha = 0.05, beta = 0.20, 25 clusters per arm, and 15 individuals per cluster. We calculated the detectable difference assuming a difference in differences design with baseline correlation of 0.8. All calculations use the *clustersampsi* command in Stata 14.1. We obtained a sample size of 1,125 parents/guardians at baseline and endline. Our sample is powered to detect a difference in difference of disrespectful care of 5 percentage points (from 14% at baseline to 9% at endline) or a difference in difference in communication of the child's diagnosis of 8 percentage points (from 46 to 54%).

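### The 80% power claimed for 5 and 8 points rests on a baseline correlation of 0.8 that does not fit new samples of 15 per facility at the ICC those figures imply; the planned DID has roughly one-third power.

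*Protocol article*

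**What the plan says.** The section on sample size estimation in the protocol article fixes the design "given alpha = 0.05, beta = 0.20, 25 clusters per arm, and 15 individuals per cluster". It describes the calculation as "using baseline prevalence and intraclass correlation coefficients (ICC) determined from the prior studies", but prints no ICC. It adds: "We calculated the detectable difference assuming a difference in differences design with baseline correlation of 0.8". The result is given as "Our sample is powered to detect a difference in difference of disrespectful care of 5 percentage points (from 14% at baseline to 9% at endline", and for the second indicator as "communication of the child's diagnosis of 8 percentage points (from 46 to 54" percent. On numbers: "We obtained a sample size of 1,125 parents/guardians at baseline and endline", which is 75 × 15.

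The section on participants and selection criteria makes a parent or guardian eligible when accompanying a child "for a sick child outpatient visit at a study facility on a day when we are recruiting patients". The study design section has research assistants approach people after their appointment and repeats the same format at endline. The only re-contact described is a phone survey of a subset of endline respondents one to two weeks later. The analysis section makes a DID regression with facility-clustered errors primary and an endline-only comparison a sensitivity analysis.

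**The concern.** A baseline correlation of 0.8 would be unremarkable if the same people were interviewed twice about something stable, or if facility means were based on large samples. Neither fits here. Each round takes 15 visitors per facility, and nothing describes following baseline respondents to endline. What links the rounds is the facility's underlying level, and a mean of 15 binary answers is a noisy measure of it.

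The 0.8 carries the whole power claim. Without it, 375 people per arm fall well short of 80% power for either difference, even with no clustering. If it does not hold, the trial is much less sensitive than stated on the two indicators used to size it, and a non-significant result on either says much less about effects of 5 or 8 points than the paragraph suggests.

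**Working it through.** **Inputs from the protocol.** 25 facilities per arm, 15 respondents per facility per round (375 per arm per round), alpha 0.05, power 80%, r = 0.8, 14% to 9%, 46% to 54%.

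**Assumptions.** Two-sided test (1.960 + 0.842 = 2.802). The ICC is not given, so it is back-solved and varied. Stability means the between-round correlation of true facility levels.

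**1. Reproducing the stated figures.** Individually randomised n per arm = 2.802² × [p0(1−p0) + p1(1−p1)] / d².
- Disrespect: 7.85 × (0.1204 + 0.0819) / 0.05² ≈ 635.
- Diagnosis: 7.85 × (0.2484 + 0.2484) / 0.08² ≈ 609.

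Only 375 are available. An endline-only comparison at ICC 0 has standard errors √(0.2023/375) = 0.0232 and √(0.4968/375) = 0.0364, giving 58% and 59% power. Reaching 80% therefore depends on the 0.8.

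The software's adjustment is not shown, so two plausible factors f were tried: 1−r² = 0.36 and 2(1−r) = 0.40. Setting n·(1+14·ICC)·f = 375:
- f = 0.36: 375/(635×0.36) = 1.640, so ICC = 0.640/14 = 0.046. Diagnosis: 1.710, so ICC = 0.051.
- f = 0.40: 1.476, so ICC = 0.034. Diagnosis: 1.539, so ICC = 0.038.

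The stated differences are thus reproducible with r = 0.8 and an ICC of about 0.03-0.05.

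**2. The correlation new samples can give.** For facility means of 15, r = 15·ICC·stability/(1+14·ICC), largest when stability is 1.
- ICC 0.034: 0.51/1.476 = 0.35.
- ICC 0.046: 0.69/1.644 = 0.42.
- ICC 0.051: 0.765/1.714 = 0.45.

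For r = 0.8 with stability 1: 0.8 + 11.2·ICC = 15·ICC, so ICC = 0.8/3.8 = 0.21. With stability 0.9: 0.8/2.3 = 0.35.

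At ICC 0.21 the design effect is 1 + 14×0.21 = 3.94. Keeping r = 0.8 and f = 0.36, the disrespect standard error is 0.0232 × √(3.94×0.36) = 0.0277, giving 44% power; diagnosis gives 45%. With f = 0.40 they are 40% and 42%. Under these forms, no ICC supports both the 0.8 and the stated differences.

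**3. Power of the planned DID, without the software formula.** Let v(p) = p(1−p)(1+14·ICC)/375, with the control arm at p0 in both rounds. Then Var(DID) = 2·v0·(1−r) + v0 + v1 − 2r√(v0·v1), and power = Φ(d/SE − 1.96).

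At ICC 0:
- Disrespect: SE = √[(3×0.1204 + 0.0819)/375] = 0.0344; Φ(1.455−1.96) = 31%.
- Diagnosis: SE = √(4×0.2484/375) = 0.0515; Φ(1.554−1.96) = 34%.

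| ICC | Stability | r | Power, 5 points | Power, 8 points |
|---|---|---|---|---|
| 0 | 1 | 0 | 31% | 34% |
| 0.05 | 1 | 0.44 | 32% | 36% |
| 0.05 | 0.8 | 0.35 | 28% | 32% |
| 0.10 | 1 | 0.63 | 33% | 37% |
| 0.21 | 1 | 0.80 | 36% | 42% |
| 0.30 | 1 | 0.87 | 40% | 46% |

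A beta-binomial simulation (20,000 runs) at ICC 0.045-0.05 gave 30-32% and 34-36%.

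**4. Detectable differences at 80% power.** Solve d = 2.802·SE(d), with the endline variance taken at p0 − d or p0 + d.
- Disrespect, ICC 0: at d = 0.0923 the endline rate is 4.77%, SE = √[(0.3612+0.0454)/375] = 0.0329, and 2.802×0.0329 = 0.092. At ICC 0.05: 9.15 points with stability 1 and 9.8 with stability 0.8.
- Diagnosis: about 14.4 points (ICC 0), 14.0 (ICC 0.05, stability 1) and 15.0 (ICC 0.05, stability 0.8).

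**The case against.** Several points on the other side stand.

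- A reader might infer that samples of 15 can never give a correlation of 0.8. The documents do not support that. The ICC is unstated, and 0.8 is attainable at an ICC of about 0.21 or more if facility levels do not change. What fails is the combination of 0.8 with the stated differences.
- A reader might infer an arithmetic slip. Given r = 0.8, the figures reproduce at an ordinary ICC. The fault is the assumption fed into the calculation.
- The implied ICC of 0.03-0.05 depends on an adjustment formula that the article does not give. Both plausible forms lead to the same place, and the DID power in step 3 uses neither.
- The figures for ICC 0-0.05 are not a ceiling. With perfect stability, power rises with the ICC, but only to 40% and 46% at ICC 0.30; with lower stability it falls below 30% for disrespect.
- New respondents are inferred from visit-based recruitment; the article never says the samples are independent. The inference is strong, since no follow-back is described and chance overlap would not produce a correlation near 0.8.
- The study is labelled proof of concept, and nothing says a null result will be read as excluding 5 or 8 points. The calculation also concerns two single indicators, not the planned composites. This limits the consequence but does not make the stated power correct.

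Reading 0.8 as facility stability does not rescue the claim: at ICC 0.05 it gives 28% and 32%. Nor does a one-sided test, at about 44% and 48%.

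**Conclusion.** The power statement is wrong as written. For the recruitment and primary analysis the protocol describes, power is about 31-32% for the 5-point difference and 34-36% for the 8-point difference at ICC 0-0.05 with perfectly stable facilities. It is 28% and 32% with stability 0.8 at ICC 0.05, and 36% and 42% at ICC 0.21 with perfect stability. Under the first set of conditions, a true effect of the stated size on either indicator would be missed about two times in three.

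This rests on new respondents in each round, a two-sided 5% test, 15 completed interviews per facility per round, and control-arm rates that stay at baseline. It does not extend to the composite indicators, whose power the article does not address.

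**What to change.** In the sample size section, drop the correlation of 0.8 or replace it with one that new samples of 15 can give, namely 15·ICC·stability/(1+14·ICC). State the ICC taken from the prior studies and the facility stability assumed. Restate the 80%-power detectable differences for the DID as about 9-10 points for disrespectful care and about 14-15 points for communication of the diagnosis at ICC 0-0.05, and re-solve them once the actual ICC is entered. Say that respondents are newly sampled in each round, if that is so. Interpret non-significant results by their confidence intervals.

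Figures for an analysis adjusting for the facility baseline mean should appear only if that model is adopted, and should be solved with the variance at the detectable endline rate.

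The cost is a less favourable stated sensitivity. No extra participants, facilities or data collection are needed.

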### Measures

The primary outcome of interest is patient experience. To develop measures of patient experience we drew from the literature on respectful maternal care (31), health systems responsiveness (32, 33), and patient experience (34). The final survey questions include previously used measures of disrespectful care in Tanzania and international surveys of patient experience conducted in sub-Saharan Africa by the World Health Survey and the Service Provision Assessment (10, 33, 35, 36). We also take advantage of publically available and widely used measures from the U.S (30). These indicators are refined and expanded based on our qualitative work. Patient experience includes aspects of patient dignity, autonomy, confidentiality, communication, timely attention, and social support (32, 37). Composite indicators of patient experience will be developed from the individual indicators in order to represent the main sub-domains, specifically for effective communication and respectful care.

Secondary outcomes are measured through the parent/guardian survey, the parent/guardian follow-up survey, and the healthcare provider surveys. From the parents/guardians we will measure their utilization behavior, rating of technical quality, such as the providers' medical knowledge, satisfaction with care, likelihood of recommending the health facility, rating of overall quality, child's illness resolution, and confidence in the health system. From the healthcare providers, we measure attentiveness to patient experience, value of patient experience, perceptions of the quality of care they provide, job satisfaction, stated motivation, and attrition.

### Analysis

The primary causal identification strategy for the intent to treat analysis will be a difference-in-differences (DID) analysis comparing change in outcomes in the intervention groups to changes in outcomes in the control group. DID analyses have the advantage of controlling for differences between the groups at baseline. We will use the following model:

$$\begin{array}{l} Y_{if}=\;\mu +\;\gamma \cdot Private_{if}+\lambda \cdot T_{if}+\;\delta \cdot (Private_{if}\cdot T_{if})\\ \;+\eta \cdot Reward_{if}+\nu \cdot (Reward_{if}\cdot T_{if})+\varepsilon_{if} \end{array}$$

Here, *Y*_*if*_ is the outcome for individual *i* in facility *f*, μ is the mean outcome among individuals in the control facilities at baseline, γ is the mean difference between individuals in the intervention groups and control group at baseline, λ is the effect of time (T is a post intervention indicator), and δ and η are the estimators of interest: the difference between the change in the private or reward intervention groups and the change in the control group, respectively. ε_*if*_ is the individual error clustered at the facility level. We will conduct a sensitivity analysis assessing endline differences only and one imputing missing data. Additional secondary analyses will use discrete choice data and free-list responses from the providers to assess their views on quality of care. These analyses will allow us to assess if providers are inattentive to patient experiences or if they do not think that they are important, and if this changes as a result of the intervention.

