### Randomization

After baseline data collection, we will stratify study facilities by district. Within each stratum, we will randomize the facilities to one of three arms: private feedback (intervention), social recognition reward (intervention), or no feedback (control) with a 1:1:1 allocation ratio. The principal investigator will conduct randomization using a random number generator in Stata version 14.2. Parents/guardians will be recruited from the health facilities that they visit and assigned that facility's intervention status. Healthcare providers will likewise be assigned the intervention status of the facility where they work. Participants will not be blinded to the allocation. It is possible that healthcare providers in the control group, or the private feedback group, will learn about the interventions provided in the other arms. This is however unlikely given the short duration of the study. If they do learn of the interventions in the other arms and this causes them to improve the care they provide, this could lead to a dilution of effect.

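### The primary difference-in-differences analysis is valid but less precise than an endline analysis adjusted for each facility's baseline mean

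*Protocol article*

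**What the plan says.** All places are in the protocol article.

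- **Randomization.** Allocation follows the first survey round: "After baseline data collection, we will stratify study facilities by district", and facilities are then allocated "with a 1:1:1 allocation ratio".
- **Analysis.** "The primary causal identification strategy for the intent to treat analysis will be a difference-in-differences (DID) analysis". The printed equation has arm, time and arm-by-time terms only, and its error term "is the individual error clustered at the facility level". The reason given is that "DID analyses have the advantage of controlling for differences between the groups at baseline". An endline comparison appears only in a secondary role: "We will conduct a sensitivity analysis assessing endline differences only and one imputing missing data".
- **Sample size estimation.** Detectable differences of 5 points (14% to 9%) and 8 points (46% to 54%) are "given alpha = 0.05, beta = 0.20, 25 clusters per arm, and 15 individuals per cluster", with a baseline correlation of 0.8. ICCs are said to come from prior studies, but no value is printed.
- **Participants and selection criteria.** Respondents are caregivers attending on recruiting days. The two rounds are therefore separate samples, linked only through the facility.

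**The concern.** Controlling for baseline differences is a strong reason for DID when groups were not randomised. Here they were, and after the baseline data were in hand. Any baseline gap between arms is chance, and only part of it should be expected to persist to endline. The part that persists is the regression slope of the endline facility mean on the baseline facility mean. DID fixes that slope at 1.

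With 15 different respondents per round, much of the variation between baseline facility means is sampling noise, so the slope is likely to be well below 1. If it is 0.4, a chance gap of 4 points would persist as 0.4 × 4 = 1.6 points, yet DID removes all 4. Averaged over randomisations this cancels and causes no bias, but it adds variance. What is at stake is precision that the planned data could supply at almost no cost.

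**Working it through.** **Inputs.** From Sample size estimation: k = 25 facilities per arm, m = 15 per facility per round, alpha 0.05, power 80%, correlation 0.8, differences 14→9% and 46→54%. Assumptions: alpha is two-sided (the article does not say). The ICC is unknown. The stability s of true facility levels between rounds is unknown, so s = 1 and s = 0.8 are both shown.

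**Step 1. The plan's own figures.** 3 × 25 × 15 = 1,125 per round, which reproduces. The detectable differences cannot be reproduced directly without the ICC, so I solve for it. The pooled two-proportion formula gives 638 per arm for 14→9% and 613 for 46→54% under individual sampling. With 375 per arm and a baseline factor f, the design effect is 375/(n·f), and ICC = (design effect − 1)/14.

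| Difference | f = 2(1−0.8) = 0.40 | f = 1−0.8² = 0.36 |
|---|---|---|
| 14→9% | 1.469, ICC 0.034 | 1.633, ICC 0.045 |
| 46→54% | 1.529, ICC 0.038 | 1.699, ICC 0.050 |

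Across pooled, unpooled and continuity-corrected formulas the range is 0.027 to 0.051.

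**Step 2. Relative variances.** With r the correlation of baseline and endline facility means and endline-only set to 1, DID has 2(1−r) and ANCOVA has 1−r². Their difference is 2(1−r) − (1−r²) = (1−r)² ≥ 0, so in large samples ANCOVA is never less precise than DID, whatever the ICC. The ratio DID/ANCOVA is 2/(1+r).

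**Step 3. The value of r.** With separate samples, r = m·ICC·s/(1+(m−1)·ICC).

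| ICC | s | r | DID | ANCOVA | DID/ANCOVA |
|---|---|---|---|---|---|
| 0.03 | 1 | 0.317 | 1.366 | 0.900 | 1.52 |
| 0.03 | 0.8 | 0.254 | 1.493 | 0.936 | 1.60 |
| 0.05 | 1 | 0.441 | 1.118 | 0.805 | 1.39 |
| 0.05 | 0.8 | 0.353 | 1.294 | 0.875 | 1.48 |
| 0.0625 | 1 | 0.500 | 1.000 | 0.750 | 1.33 |
| 0.10 | 0.8 | 0.500 | 1.000 | 0.750 | 1.33 |
| 0.2105 | 1 | 0.800 | 0.400 | 0.360 | 1.11 |

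The break-even between DID and endline-only is r = 0.5, which means ICC 0.0625 at s = 1 and 0.10 at s = 0.8.

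**Step 4. Power.** Example: 46→54%, ICC 0.05, s = 1. The effective number per arm is 375/1.70 = 220.6, which is divided by the relative variance: 197.3 for DID, 220.6 for endline-only, 274.0 for ANCOVA. For DID, z = (0.08·√197.3 − 1.96·√0.5)/√0.4968 = −0.372, a power of 35.5%. The same step gives 39.0% for endline-only and 46.5% for ANCOVA. Over the Step 1 ICCs and both values of s:

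| Difference | DID | Endline-only | ANCOVA |
|---|---|---|---|
| 14→9% | 30.6–34.2% | 39.0–42.3% | 42.9–46.9% |
| 46→54% | 31.4–35.5% | 39.0–42.4% | 43.5–47.9% |

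**Step 5. Simulation.** I used 25 facilities in each of two arms, 15 per round, beta-binomial responses and 4,000 runs per setting. At prevalence 14%, ICC 0.043, s = 1, the standard errors were 0.0352 (DID), 0.0327 (endline-only) and 0.0298 (ANCOVA). At 46%, ICC 0.05, s = 1, they were 0.0497, 0.0483 and 0.0433. The order agrees. The DID/ANCOVA variance ratios, (0.0352/0.0298)² = 1.40 and (0.0497/0.0433)² = 1.32, are slightly below the formula values of 1.43 and 1.39.

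**The case against.** **The ICC is not in the article.** It is recovered by granting the 0.8 correlation, which the recovered ICC then shows to be out of reach for means of 15. This is fair. The back-solve estimates what was entered in the calculation, not what is true, so every size that depends on it is conditional. With one-sided alpha the implied ICC is 0.052–0.084, and rounding of the detectable differences could raise it to about 0.073. The inequality in Step 2 needs no ICC and is untouched.

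**Taken at face value, 0.8 favours DID.** If it is the correlation of observed facility means, DID (0.40) clearly beats endline-only (1.00), and the ANCOVA gain shrinks to √(0.40/0.36) = 1.054, about 5% in standard error. With 15 separate respondents per round this needs an ICC of at least 0.8/3.8 = 0.21. There, even with stable facilities, DID power for the stated differences is only about 40%. The 0.8 and the stated differences therefore do not fit together, but that is a sample-size matter.

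**Is the endline-only sensitivity analysis more powerful than the primary?** A reader might infer this as a general fact, but the article does not support it. It holds at ICCs of 0.03–0.05 and reverses once r exceeds 0.5. At ICC 0.073 with stable facilities, simulation gives standard errors of 0.0509 for DID and 0.0517 for endline-only.

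**Is DID biased, or its stated rationale false?** A reader might infer this too. Neither is so: DID is unbiased over randomisation, it does control for baseline differences, and it matches the design assumed for the sample size. The sentence merely gives no reason to prefer DID to baseline adjustment.

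**The article is condensed.** District terms and other covariates may sit in the full plan, so their absence carries little weight here. The choice of DID as primary is stated outright.

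**Conclusion.** The point holds as one of efficiency. The named primary estimator is valid, but in large samples it is never more precise than an endline analysis adjusted for the baseline facility mean. If the ICC is about 0.03–0.05 with two-sided alpha, the DID variance is about 1.4–1.6 times that of ANCOVA by formula, and power is roughly 31–36% against 43–48%. If facility means really correlated at 0.8, the loss would be about 5% in standard error. The direction is firm, while the size rests on an unprinted ICC and on how stable facilities are between rounds.

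It would be tempting to blame the estimator for the whole gap to the stated 80%. That is not supported, because ANCOVA also falls well short at these ICCs. Most of the gap comes from the 0.8 assumption in the sample-size section.

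**What to change.** Make the primary analysis the endline outcome regressed on the Private and Reward indicators, the facility's baseline mean of that outcome and the district strata, with facility-clustered errors. A mixed model with a common baseline mean across arms, and facility and facility-by-period random effects, would serve equally well. Keep the DID model as a sensitivity analysis. Print the ICCs and say at which level the 0.8 applies, so that the gain can be judged.

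The cost is one changed model, about one degree of freedom for the baseline mean and three for the four districts, out of 75 facilities. The effect would no longer carry the DID label. No further data collection is needed. The change recovers precision but does not by itself bring power to 80%.

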## Methods and analysis

### Study area

The study is being conducted in four rural districts of Pwani Region, Tanzania (Bagamoyo, Kibaha Rural, Kisarawe, and Mkuranga). Sixty-seven percent of the population in the region resides in rural communities, where health services are primarily delivered through dispensaries and health centers. Estimates for literacy rate in the region in 2002 were as low as 50% in rural areas and 69% in urban areas (23). Data from the Demographic and Health Survey indicate that this area is one of the poorer areas in Tanzania, with 53.7% of the population in the bottom two wealth quintiles, and only 1% of the rural Pwani population in the highest wealth quintile (24).

Tanzania Health Promotion Support (THPS), a local non-governmental organization supporting this study, currently supports government-managed health facilities in the study districts. Study facilities are government-managed, THPS-supported, primary care clinics (dispensaries) that had at least 450 sick child visits during the period from October 2016-June 2017. In one district, we included two facilities with fewer than 450 visits in order to have a minimum of 15 facilities per district. We selected primary care clinics (known as dispensaries in Tanzania) for the study, because they are the lowest level of the Tanzanian health system that is expected to provide outpatient care for sick children and are embedded within their communities and thus most likely to be responsive to community feedback (25).

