**Figure 2 F2:**
[figure not shown]
Outline of the BASI study design.

The study includes two rounds of data collection, baseline, and endline, at the 75 selected health facilities. We will use two methods of data collection for the parent/guardian surveys. In one district, we will conduct phone interviews. Research assistants will approach parents/guardians after their appointment with the healthcare provider and read a brief recruitment script, which introduces the interviewer, states the main aim of the study, describes why they are being recruited to participate in this survey (i.e., the eligibility criteria), and assurance of confidentiality. If the participants are eligible and agree to participate in the interview 2–7 days later, the research assistants will obtain written consent at the time that their phone number is collected and then follow-up with a phone call. Written consent gives a detailed description of the study, including their rights as a participant. For participants who do not have a phone number to give, we will provide our study phone number and encourage them to “beep” us from any number they have access to in the following 2–7 days. When we receive phone calls, we will return them to complete the survey. In the remaining three districts, parent/guardian surveys will be collected as exit surveys. For exit surveys, research assistants will approach caregivers after their visit with the healthcare provider and inform them of the study. If they express interest, the research assistant will invite them to a private space away from the health facility to further inform them of the study using a recruitment script as described above. A full informed consent will be obtained prior to participation in the study.

At both baseline and endline we will also interview healthcare providers at the study facilities. They will be invited to participate in a structured interview that will include questions on socio-demographics, their job satisfaction, and their opinions on quality of care including a free list exercise in conjunction with a discrete choice experiment. Healthcare providers will be informed that their facility is participating in a study and that are being invited to participate in a survey that will help researchers learn about people's experience with healthcare and how providing feedback to health workers can help them better serve their communities.

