Baseline results will be delivered to intervention facilities after all baseline data collection is complete. Approximately 4–7 weeks after the baseline results have been delivered to the intervention facilities, we will conduct the endline surveys. These will be collected from all study facilities in the same format as outlined above (phone surveys in one district and exit surveys in in three districts). In addition, at endline, in order to measure the effect of negative patient experiences on health outcomes and patient behavior, we will interview a subset of parents/guardians by phone ~1–2 weeks after their primary visit. We will ask them about the health of the study child and additional questions about recent illness among their children and their care-seeking behaviors. However, this study is a proof of concept to detect changes in provider behavior and is not necessarily powered to detect differences in these secondary outcomes. Participants for the follow-up survey will be randomly selected from those who complete the endline parent/guardian survey.

The populations living in the study districts are low-literacy and economically disadvantaged as a whole. We therefore expect that study participants will also be low-literacy and economically disadvantaged. All survey materials are written in language that is understandable to low-literacy populations in the local language (Swahili), and were pilot tested for clarity. The surveys will all be conducted by Swahili-speaking Tanzanian research assistants who have experience working with similar populations. The qualitative data collection conducted prior to the start of the cRCT focused on ensuring that survey questions were understandable to this population. All data will be collected using hand-held tablets with the SurveyCTO software. Data will be encrypted to protect confidentiality. All research assistants will undergo training in data collection methods, including privacy, and confidentiality of participants and their data.

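### Randomisation is stratified by district and interview mode follows district, but the printed model has no district terms: harmless in the DID if district effects are stable, conservative otherwise and in an endline-only analysis that also omits district

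*Protocol article*

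**What the plan says.** - **Stratification.** Randomization section: "After baseline data collection, we will stratify study facilities by district"; then "Within each stratum, we will randomize the facilities to one of three arms", "with a 1:1:1 allocation ratio".
- **Interview mode.** Study design and methodology: "In one district, we will conduct phone interviews", with the call 2–7 days after recruitment at the facility. "In the remaining three districts, parent/guardian surveys will be collected as exit surveys". On the endline surveys: "These will be collected from all study facilities in the same format as outlined above". Mode is therefore tied to district and does not change between rounds.
- **District sizes.** Study area gives four districts and says two smaller facilities were admitted "in order to have a minimum of 15 facilities per district". No other district counts are given.
- **Model.** Analysis section: "We will use the following model". The equation has an intercept, two arm indicators, a post-intervention indicator, two arm-by-time products and an error clustered by facility. It contains no district or mode term.
- **Endline-only analysis.** It is named once, in the Analysis section, as a sensitivity analysis. No equation is given for it.

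**The concern.** Stratified allocation balances districts across arms, so differences between districts contribute little to the true sampling variation of the arm contrasts. A model without the strata leaves those differences in the residual. The reported standard error can then exceed the true one, giving intervals that are too wide and tests that reject less often than 5% under the null.

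District matters more than usual here because it also carries interview mode: a phone call days after the visit may draw different answers from an exit interview. At stake is precision in the primary DID. For the endline-only check, inflated intervals could make it appear not to support the DID for reasons unrelated to the intervention.

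**Working it through.** **The plan's own figures.** 3 arms × 25 facilities × 15 interviews = 1,125 per round, as stated. The Sample size estimation section gives alpha 0.05, 80% power and a baseline correlation r of 0.8, but not the ICC values. Taking a two-sided test, a design effect of 1 + 14 × ICC and a factor 1 − r² = 0.36, the stated differences reach 80% power at an ICC of about 0.046 (14% to 9%) and 0.051 (46% to 54%). Check against 375 per arm: 638 × 0.36 × (1 + 14 × 0.0457) ≈ 377, and 613 × 0.36 × (1 + 14 × 0.0507) ≈ 377, where 638 and 613 are the numbers needed per arm under individual randomisation.

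**Formulas for the excess.** Let s² = p(1 − p), τ² = ICC × s², w the share of facilities in the phone district and d the shift in that district.

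- Endline facility-mean variance within district: V = τ² + (1 − ICC)s²/15. Variance left in the residual if district is omitted: D = w(1 − w)d². SE ratio = √((V + D)/V).
- DID, variance of a facility's change: V′ = 2τ²(1 − 0.8) + 2(1 − ICC)s²/15, reading 0.8 as the facility correlation between rounds (an assumption). A stable shift adds nothing, so the ratio is 1. If half of d arises between rounds, the ratio is √((V′ + D/4)/V′).

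**Worked case.** p = 0.46, ICC = 0.05, w = 0.20, d = 0.10:

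- s² = 0.2484, τ² = 0.01242, V = 0.01242 + 0.01573 = 0.02815, D = 0.16 × 0.01 = 0.0016. Endline ratio = √(1.0568) = 1.028.
- V′ = 0.00497 + 0.03146 = 0.03643, D/4 = 0.0004. DID ratio = √(1.0110) = 1.005.

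**Range** (p = 0.14 and 0.46, ICC 0.02–0.10, w = 20–25%):

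| Assumed phone-district shift | Endline-only SE excess | DID excess, stable shift | DID excess if half the shift arises between rounds |
|---|---|---|---|
| 5 points | 0.5–2% | 0 | 0.1–0.4% |
| 10 points | 2–9% | 0 | 0.5–1.4% |
| 20 points | 8–32% | 0 | 2–5.5% |

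With 75 facilities and at least 15 per district, the phone district could hold up to 75 − 3 × 15 = 30 facilities (40%). Then w(1 − w) is 0.24 instead of 0.16, and the worked case rises from 1.028 to √(1 + 0.0024/0.02815) = 1.042.

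**Simulation in SD units** (1,500 runs per scenario; districts of 15/18/20/22, ICC 0.05, facility correlation 0.8, facility-clustered errors):

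- Stable 0.5 SD shift, DID: mean SE 0.1099 with and without district main effects, empirical 0.1090, type I error 5.1% for both.
- Same shift, endline-only: 0.1118 without district, 0.0942 with it, empirical 0.0939. 0.1118/0.0939 = 1.19; type I error 2.5% without and 5.7% with. For a 0.3 SD shift: 0.1022/0.0945 = 1.08.
- Extra 0.5 SD at endline, DID: 0.1230 against an empirical 0.1102, ratio 1.12, type I error 3.1%. District main effects leave it at 0.1231; district-by-time terms bring it to 0.1070.

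**Simulation on a 46% outcome** (3,000 runs per scenario; districts of 15/18/21/21, ICC 0.03):

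- No district-by-time shift, DID: true SD 0.0503, mean SE 0.0504.
- District-by-time shifts up to ±5 points plus a 10-point mode shift: excess 1% (DID) and 9% (endline-only).
- Shifts up to ±10 points plus a 20-point mode shift: DID 0.0539/0.0491 = 1.10, type I error 3.4%; endline-only 0.0589/0.0422 ≈ 1.40, type I error 0.8%. With district terms: 0.0492 against 0.0491, and 0.0421 against 0.0422.

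**The case against.** The strongest reply is that the printed equation is the DID, and for the DID the omission does no harm unless districts move apart between rounds. Nothing in the article suggests they do: mode is the same in both rounds, and endline follows feedback by only about 4–7 weeks. This stands. A reader might infer that the primary standard error is too large as a matter of course; both simulations show it is correct under stable district effects.

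Second, the larger excesses belong to a sensitivity analysis for which no equation is printed, and its covariates may sit in a fuller document. This also stands, so that part of the point is conditional. It does not cover the primary model, which is printed in full without the stratification factor.

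Two stronger readings should be resisted:

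- **That the trial is already short of power, so the loss is serious.** The stated detectable differences are attainable at ICCs of about 0.05 under the article's own correlation. The ICCs are not given, so neither a shortfall nor adequacy can be shown here.
- **That mode differences leak into the DID when interview numbers per facility change, for example through phone non-response.** With numbers varied from 8 to 22 per facility per round, the DID SE was about 2% larger without district terms (0.1145 against 0.1123) and still matched its empirical value. Bias between arms would need numbers to shift differently by arm, which the article does not suggest.

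**Conclusion.** The point holds as a minor efficiency matter: the printed analysis does not follow the stratified design, and correcting it is nearly free. Allocation is randomised 1:1:1 within district, so omitting district causes no bias, and any error is in the conservative direction.

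- **Primary DID:** standard error essentially correct if district and mode effects are stable. Otherwise it is about 0–5% too large for moderate assumed between-round shifts and 10–12% for large ones. The documents neither show nor exclude such shifts.
- **Endline-only analysis, if it also omits district:** about 0.5–2%, 2–9% and 8–32% too large for mode shifts of 5, 10 and 20 points. The ratio near 1.4 comes from an extreme scenario and should not be taken as expected.

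All magnitudes depend on assumed district sizes (only the minimum of 15 is stated), ICCs and district or mode shifts. The tabulated ranges take 20–25% of facilities in the phone district and would be larger if it held more.

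**What to change.** In the primary model, add three district indicators and three district-by-time terms. The district-by-time terms do the work; main effects alone leave the DID standard error unchanged. State that the endline-only model includes the three district indicators. Because mode is determined by district, no separate mode term is needed.

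The cost is six terms in the DID and three in the endline-only model, with district already recorded for every facility and no further data collection. If a fuller analysis plan already contains these terms, the article's equation need only be brought into line with it.
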